## Abstract

**Background:**

Up to 33% of women develop symptoms of posttraumatic stress disorder (PTSD) after a traumatic birth experience. Negative and traumatic childbirth experiences can also lead to fear of childbirth, avoiding or negatively influencing a subsequent pregnancy, mother-infant bonding problems, problems with breastfeeding, depression and reduced quality of life. For PTSD in general, eye movement desensitization and reprocessing (EMDR) therapy has proven to be effective. However, little is known about the preventive effects of early intervention EMDR therapy in women after a traumatic birth experience. The purpose of this study is to determine the effectiveness of early intervention EMDR therapy in preventing PTSD and reducing PTSD symptoms in women with a traumatic birth experience.

**Methods:**

The PERCEIVE study is a randomized controlled trial. Women suffering from the consequences of a traumatic birth experience will be randomly allocated at maximum 14 days postpartum to either EMDR therapy or ‘care-as-usual’. Patients in the EMDR group receive two sessions of therapy between 14 (T0) and 35 days postpartum. All participants will be assessed at T0 and at 9 weeks postpartum (T1). At T1, all participants will undergo a CAPS-5 interview about the presence and severity of PTSD symptoms. The primary outcome measure is the severity of PTSD symptoms, whereas the secondary outcomes pertain to fear of childbirth, mother-infant bonding, breastfeeding, depression and quality of life. The study will be conducted at a large city hospital and at multiple midwifery practices in Amsterdam, the Netherlands.

**Discussion:**

It is to be expected that the results of this study will provide more insight about the safety and effectiveness of early intervention EMDR therapy in the prevention and reduction of PTSD (symptoms) in women with a traumatic birth experience.

**Trial registration:**

Netherlands Trial Register NL73231.000.20. Registered on 21 August 2020.

## Background

According to recent meta-analyses, 3–4% of all women develop PTSD following childbirth [1, 2] while up to 33% of women experience symptoms of PTSD [3, 4]. Risk factors for a traumatic birth experience are diverse. Prevalence of traumatic birth experiences has been found to be higher among women with unexpected interventions during labour and delivery, such as unplanned caesarean section or vacuum-assisted delivery [3, 5]. However, medically uncomplicated deliveries may also be perceived as traumatic [3, 5–8]. A Dutch retrospective survey analysing the perception of over 2000 women with a self-reported traumatic birth experience showed that lack, or loss, of control (54.6%), and fear for their baby’s health or life (49.9%), followed by high intensity of pain or physical discomfort (47.4%) attributed significantly to the traumatic aspect of this experience [9]. Other reported risk factors include a history of psychiatric illness, previous trauma, fear of childbirth (FoC) and preeclampsia [2, 5].

According to the Dutch Society of Obstetrics and Gynaecology (NVOG) guidelines on birth-related PTSD (symptoms) [10] and the National Institute for Health and Care Excellence (NICE) treatment guidelines [11], a traumatic birth experience is defined as ‘the (subjective) experience and interpretation of a woman with or without satisfying diagnostic criteria of the Diagnostic and Statistical Manual of Mental Disorder (DSM-) 5 for PTSD’ [10, 11]. DSM-5 criteria of PTSD include symptoms of re-experiencing, avoidance and numbing, negative cognitions and mood and hyperarousal [12]. Symptoms may resolve naturally, but in some cases may lead to a chronic mental health condition [13]. To meet the diagnostic criteria for PTSD, symptoms must last longer than 1 month and result in significant dysfunction. However, due to similarity with physiological symptoms associated with a major life event, such as becoming a parent, PTSD (symptoms) are often not well recognized. Additionally, PTSD can be confused with postpartum depression because of a diagnostic overlap in symptoms such as negative cognitions, or co-occurrence of both disorders [13].

Besides PTSD, exposure to a negative or traumatic childbirth frequently results in fear of childbirth (FoC), avoiding a subsequent pregnancy, reduced quality of life (QoL), problems with breastfeeding and depression [5, 14–17]. A birth-related trauma causing distress during a subsequent pregnancy has also been found to be related to both maternal and foetal negative outcomes, such as avoiding prenatal care, demanding a planned caesarean section, and preterm birth [18–21]. Furthermore, traumatic birth experiences may negatively influence the mother-infant bonding with studies showing that children from parents with PTSD express a more avoidant attachment style, caused by feelings of rejection and anger towards the infant [22, 23]. Mother-infant bonding and early attachment proves essential for the infants’ future self-esteem and resilience, emotion regulation and their ability to form close relationships [24, 25]. Conversely, studies have shown that the presence of PTSD in parents is associated with the development of psychopathology and higher rates of anxiety and behavioural problems in their offspring [14, 26]. Moreover, it may impair early cognitive development of the infant [27]. To this end, it is conceivable that preventing PTSD, or alleviating PTSD symptoms, reduces the likelihood of mother-infant bonding difficulties, thereby exerting a positive effect on both the mother and a ‘butterfly effect’ on the infant to create a healthier adult in later life [26]. Hence, research that would identify a short-term and cost-effective postpartum intervention is important.

Regarding the treatment of PTSD in general, meta-analyses and treatment guidelines recommend eye movement desensitization and reprocessing (EMDR) therapy as one of the first-line therapies for this mental health condition [8, 28–30]. Additionally, encouraging results have been reported with early EMDR interventions after traumatic events to reduce PTSD-related symptoms [31, 32]. Although the definition of early intervention varies between guidelines, a timeframe of treatment within 3 months after the traumatic incident is mostly considered to be early intervention [32]. However, a recent review on EMDR therapy studies concluded that ‘research is needed to evaluate prevention of PTSD, with clinician-administered diagnostic measures (e.g., CAPS-5) administered to treated and nontreated individuals’ (p. 245) [33]. Recently, a randomized controlled pilot study was performed among women with a traumatic birth experience aimed to study the effect of EMDR therapy on symptoms of PTSD directly postpartum in comparison with treatment as usual, which consisted of standard psychological supportive care. The proportion of asymptomatic participants was significantly higher in the EMDR therapy group at 6 weeks postpartum (78.9% vs 39.4%, *p* = 0.020) although this effect was no longer statistically significant at 12 weeks postpartum (89.5% vs 66.7%, *p* = 0.124) [34]. Since this was a pilot study, sample size was small (*n* = 37) which could account for the lack of differences between groups at 12 weeks postpartum. This encouraging result calls for replication through a randomized controlled trial [33]. Finally, it is important to note that data on the safety of early interventions following recent trauma, particularly regarding exposure to adverse birth events, are limited [35, 36].

## Methods and design

### Aim

The main purpose of the study is to determine the safety and effectiveness of ‘early intervention EMDR’ in preventing PTSD or reducing symptoms of PTSD at 9 weeks postpartum in women with a traumatic birth experience, and to compare these results with care as usual (CAU) in women who experienced their delivery as a traumatic event. Safety is defined as the absence of all of the following adverse events: increased suicidal ideation, serious self-injurious behaviour or crisis contacts for any of the aforementioned reasons [37]. It is hypothesized that early intervention EMDR therapy is safe and that women who receive early intervention EMDR will report significantly less PTSD (symptoms) 9 weeks after the delivery compared to women who receive no treatment. Furthermore, our secondary objectives are to determine the effects of early intervention EMDR therapy on FoC, QoL, mother-infant bonding (MIB), breastfeeding and depression. It is hypothesized that early intervention EMDR will significantly reduce FoC, improve QoL and MIB, increase the success of breastfeeding and prevent or reduce depressive symptoms as compared to CAU.

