#### The EMDR therapy group

Participants in the EMDR therapy group will receive two treatment sessions between 14 and 35 days postpartum, consisting of 60 min each [39]. The EMDR therapy sessions will be conducted in an out-hospital clinic by trained psychologists who have completed both the basic and advanced EMDR therapy training course accredited by the Dutch National EMDR Association (www.emdr.nl) and have at least 1 year of experience with providing EMDR therapy. When the participant or therapist is not able to be physically present because of the COVID-19 epidemic, therapy sessions may, by exception, be conducted digitally. Digital psychological interventions during COVID-19 are supported by the American Psychiatric Association and the British Psychological Society [40, 41].

The essence of EMDR therapy is that the therapist aims to reduce the vividness and emotionality of trauma memories by asking the patient to recall the trauma memory while simultaneously making eye movements [42, 43]. The EMDR therapy will be implemented with the use of rapid deployment of sets of eye movements offered by fingers or using a light bar [39]. In case of any adverse events during the study period, the EMDR therapist will report this to the researcher and set up an individual plan with regard to the wishes and needs of the participant.

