#### The CAU group

The CAU group will receive care as provided currently which means no treatment for their traumatic birth experience. However, participants in this group will receive two telephone calls between 14 and 35 days postpartum to monitor the course of symptoms regarding their traumatic birth experience. These conversations will be conducted by the researcher. Preferably, no professional psychological treatment will be given during the study period as to not bias the results. Therefore, when a participant is stable but wishes to receive EMDR treatment, she will be asked to wait for therapy until she has filled in the last questionnaires and the Clinician-Administered PTSD Scale of DSM-5 (CAPS-5) interview is conducted at the end of the study period (T1). When symptoms of PTSD significantly worsen during the study period, women will be referred to their general practitioner who can then refer the patient to a psychologist or psychiatrist when needed. When professional psychological help regarding the birth trauma is started within the study period, this will be registered and reported as a deviation of the protocol.

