#### Safety

Safety of early intervention EMDR will be monitored by the therapist. The occurrence of all adverse events, which is defined as increased suicidal ideation, serious self-injurious behaviour or contacts with healthcare providers in case of mental health crisis, will be reported to the researcher. Safety of participants in the CAU group will be monitored by the researchers. Based on regular phone calls, it will be estimated whether additional interventions regarding their psychological symptoms are indicated. For both groups, the researcher will register the adverse event and the general practitioner will be informed to take appropriate measures to ensure the safety of the participants.

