### Statistical analysis

#### Primary study parameters

For the CAPS-5, an independent *t*-test will be performed to compare symptom severity scores between groups at T1. If the assumption of normality is violated, a Mann-Whitney *U* test will be performed. A linear mixed model analysis will determine the difference between the intervention group and the CAU group in changes in PTSD symptom severity as measured by the PCL-5 measured at inclusion and at follow-up (T0 and T1). Changes in scores of the PCL-5 will be modelled as a function of the intervention group (EMDR therapy, standard), time of measurement (T0–screening, T1 follow-up), and the interaction between time and intervention. Previous and current psychological treatment, educational level, parity, mode of delivery (vaginal birth, caesarean section, vacuum-assisted birth) and place of birth (at home, in the hospital under medical care, in the hospital under care or the midwife) will be entered as covariates. Per protocol analyses and intention-to-treat analyses will test the main effect of treatment condition, the main effect of time and the interaction effect. The assumptions of normality, homogeneity of variances and sphericity will be tested prior to interpreting the results. Furthermore, adverse events will be reported, and chi-square tests will be done to test differences in the prevalence of adverse events between the intervention and the control group.

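### The zero-event definition of safety and the planned chi-square test can disagree, neither can demonstrate safety, and events are detected and defined inconsistently

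*Protocol article*

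**What the plan says.** All references are to the protocol article.

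- **Aim.** Safety stands beside effectiveness in the main purpose. The criterion is "Safety is defined as the absence of all of the following adverse events", followed by increased suicidal ideation, serious self-injury, and crisis contacts arising from either of those. The hypothesis is "It is hypothesized that early intervention EMDR therapy is safe". No comparator, tolerated rate or margin is attached to it.
- **Primary study parameters.** Besides a plain report of the events, the only analysis named is this: "chi-square tests will be done to test differences in the prevalence of adverse events between the intervention and the control group".
- **Safety, EMDR arm.** "Safety of early intervention EMDR will be monitored by the therapist", who passes events to the researcher. The section on the EMDR therapy group adds: "In case of any adverse events during the study period, the EMDR therapist will report this to the researcher". Contact consists of two sessions: "Participants in the EMDR therapy group will receive two treatment sessions between 14 and 35 days postpartum".
- **Safety, CAU arm.** "Safety of participants in the CAU group will be monitored by the researchers", on the basis of telephone calls. The CAU section says that "participants in this group will receive two telephone calls between 14 and 35 days postpartum to monitor the course of symptoms".
- **Safety, both arms.** The researcher registers the events. Here the third event type is contact with care providers in a mental health crisis, without the restriction to suicidal ideation or self-injury made under Aim.
- **Interrater reliability and treatment fidelity.** Therapists and researchers are not blinded; the CAPS-5 interviewer is.

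**The concern.** Three things do not fit together.

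1. The definition is absolute and concerns what happens under EMDR. The test is comparative and asks whether the arms differ. The article does not say which of them decides the safety hypothesis.
2. The comparison depends on events being found equally well in both arms. A therapist who holds two 60-minute sessions and a researcher who makes two telephone calls may not find the same events, and each knows the allocation.
3. The count itself depends on which section's wording of crisis contacts is applied.

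The Background says that safety data on early intervention after recent trauma are limited, so readers are likely to rely on what this trial reports. A handful of events could be presented as a failure of safety or as no difference, depending on the rule chosen, and a difference between arms could reflect who asked.

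**Working it through.** **The plan's own figures.** The article gives no safety event rate, margin or power. Its sample size rests on the PCL-5: difference 10, SD 20, alpha 0.05, 86 per arm, power 90.3%. A two-sided two-sample t-test with 170 degrees of freedom and noncentrality 10 / (20 × √(2/86)) = 3.28 has power 0.903. Allowing for 20% loss, 86 / 0.8 = 107.5, so 108 per arm. These figures reproduce. Below, n = 86 is the number after loss and n = 108 the number randomized, per arm. **All event risks are assumptions**, because the documents give none.

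**Step 1: can the two rules disagree?** With x events under EMDR, none under CAU and n per arm, the uncorrected chi-square statistic is 2n·x / (2n − x). For n = 108:

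| EMDR vs CAU events | Statistic | Chi-square p | Fisher p | Zero-event definition |
|---|---|---|---|---|
| 1 vs 0 | 1.005 | 0.32 | 1.00 | breached |
| 2 vs 0 | 2.019 | 0.16 | 0.50 | breached |
| 3 vs 0 | 3.042 | 0.08 | 0.25 | breached |
| 4 vs 0 | 4.075 | 0.044 | 0.12 | breached |
| 6 vs 0 | 6.171 | 0.013 | 0.029 | breached |

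From one to three events the rules give opposite answers. The chi-square test first reaches p < 0.05 at 4 versus 0, where the expected count is 2 per arm; Fisher's test needs 6 versus 0. Sparse tables of this kind are where the two tests diverge.

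**Step 2: what would zero events show?** The upper end of the exact two-sided 95% interval for 0/n is 1 − 0.025^(1/n).

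- n = 86: 4.2%
- n = 108: 3.4%

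Even a result that meets the definition is compatible with a true risk of 3% to 4%.

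**Step 3: how often would the definition be breached with no added harm?** The chance of at least one event among n women is 1 − (1 − p)^n.

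| Assumed background risk p | n = 86 | n = 108 |
|---|---|---|
| 0.5% | 35% | 42% |
| 1% | 58% | 66% |
| 2% | 82% | 89% |

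**Step 4: what could the test detect?** Power by full enumeration of both binomials, at two-sided 0.05:

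| Assumed CAU vs EMDR risk | Chi-square, n = 86 | Chi-square, n = 108 |
|---|---|---|
| 1% vs 2% | 4% | 6% |
| 1% vs 3% | 12% | 16% |
| 2% vs 4% | 10% | 12% |
| 2% vs 6% | 24% | 30% |
| 5% vs 10% | 23% | 29% |

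For 2% versus 4%, Fisher's test has 3% (n = 86) or 5% (n = 108).

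**Step 5: detection and definition, side by side.**

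| | EMDR | CAU |
|---|---|---|
| Who detects | therapist, unblinded | researcher, unblinded |
| How | two sessions, days 14 to 35 | two telephone calls, days 14 to 35 |
| Who registers | researcher | researcher |

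The number of contacts, the window and the registration match. The observer and the type of contact do not. As to definition, a crisis contact unrelated to suicidal ideation or self-injury counts under Safety but not under Aim.

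**The case against.** **The definition may be meant per woman.** Aim also speaks of comparing results with CAU, so safe could mean that a woman had none of the listed events, with the proportions then compared. This is a fair reading and would remove the conflict in Step 1. The article does not state it, however, and the hypothesis is worded about the therapy without a comparator.

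**Low power for rare events is common in trials sized on efficacy.** That is true, and low power alone is not the finding. It matters here because the article states a safety hypothesis and offers no margin or interval by which to judge it. The choice of chi-square or Fisher may properly be left to an analysis plan, and Fisher's test does not cure the power. The exclusion of women with recent psychiatric illness or a recent suicide attempt makes a low event risk plausible; at 0.5%, a breach by chance among 108 women is less likely than not (42%).

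**Detection is partly harmonized.** Both arms have two contacts in the same window and the researcher registers events in both. This narrows the concern but does not equalize who asks and how.

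**Stronger readings that the text does not support.**

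- A reader might infer that no event is sought on schedule after day 35. T1 at 9 weeks is a scheduled contact, the same in both arms; therapist reporting covers the study period; the Safety section mentions regular calls without an end day; and Fig. 2 is not shown. The visible text merely does not name an adverse event enquiry at T1, which an article may leave to the full protocol.
- A reader might infer that the authors will take a non-significant test as proof of safety. No section says so.
- A reader might infer that the hypothesis cannot be tested. On the strict definition one EMDR event refutes it. What the plan cannot do is demonstrate it.

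**Conclusion.** The point holds in this form. The zero-event definition and the chi-square test are different rules, and they give opposite answers for one to three EMDR events against none. Neither can establish that EMDR is safe: zero events leaves an upper limit of 4.2% (86 women) or 3.4% (108 women), and power is about 4% to 30% over assumed CAU risks of 1% to 5% with EMDR risks two to three times as high. The upper limits and the p values depend only on the arm sizes. The power and breach probabilities rest on the assumed risks.

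Separately, the between-arm comparison is open to ascertainment bias of unknown direction and size, and the crisis-contact wording under Aim and Safety must be reconciled. This should be corrected. It does not touch the efficacy analysis or its sample size.

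**What to change.** 1. Use one adverse event definition, identical under Aim and Safety, including the scope of crisis contacts.
2. State safety as a comparison of event risk between arms in place of the zero-event criterion.
3. Add the same structured adverse event questions, covering T0 to T1, to the existing T1 questionnaire for both arms. Keep them outside the CAPS-5 interview so that its assessor stays blinded.
4. Report event counts with exact 95% confidence intervals per arm and for the risk difference. If a test is kept, use Fisher's exact test.
5. State that a non-significant test will not be taken as evidence of safety.

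**Cost.** A few items in an existing Castor questionnaire, and changes of wording. Recruitment began in September 2020, so this is an amendment that goes to the ethics committee. Women enrolled before it will have been ascertained by the old method only and should be reported separately. The safety claim becomes more modest: an estimate with its uncertainty.

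### Safety is defined as having no adverse events but analysed as a difference between arms, and no rule links the criterion to the test

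*Protocol article*

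**What the plan says.** The Aim section of the protocol article opens with: "The main purpose of the study is to determine the safety and effectiveness". It adds that results will be compared with care as usual (CAU). It then gives the criterion, "Safety is defined as the absence of all of the following adverse events", and lists worsening suicidal thoughts, serious self-harm and related crisis contacts. The hypothesis that follows is also absolute: "It is hypothesized that early intervention EMDR therapy is safe". That clause names no comparator and no acceptable rate.

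The analysis stands under Primary study parameters. Besides a plain report of the events, it plans one comparison: "chi-square tests will be done to test differences in the prevalence of adverse events between the intervention and the control group". The article does not say how the result of that test, or the observed count, leads to a conclusion that EMDR is or is not safe.

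The abstract names PTSD symptom severity as the primary outcome, and the Sample size calculation section sizes the trial on the PCL-5 alone.

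**The concern.** The criterion concerns whether any event occurs. The test concerns whether the arms differ. These are separate questions, and the same data can answer them differently.

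Taken at its word, the criterion charges EMDR with every event in a population that is already distressed, including events that would have happened without treatment. The test does account for the control arm, but failing to find a difference does not show that there is none, least of all for rare events in a trial sized for a symptom score.

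The Background section itself describes safety data on early intervention after recent trauma as limited, so readers will look to this trial for an answer. As written, that answer could depend on which section the analyst follows.

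**Working it through.** **The plan's own figure.** Difference 10, SD 20, two-sided alpha 0.05 (the sidedness is inferred). With 86 per arm the noncentrality is 0.5 × √(86/2) = 3.28, and the t-test has 90.3% power, as stated. Allowing for 20% loss, 86/0.80 = 107.5, so 108 per arm, as stated. No figure is given for safety.

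**Inputs for the safety check.** n = 108 per arm (randomised) or 86 (after the allowed loss), 1:1 allocation. The documents give no adverse-event rate, so every rate below is an assumption.

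**Step 1: chance that a harmless therapy meets the zero-event criterion.** This is (1 − p)^n, with the same true rate p in both arms.

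| Assumed rate p | n = 108 | n = 86 |
|---|---|---|
| 0.5% | 58% | 65% |
| 1% | 34% | 42% |
| 2% | 11% | 18% |
| 5% | 0.4% | 1.2% |

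The chance falls below one half when p exceeds 1 − 0.5^(1/n): 0.64% for n = 108 and 0.80% for n = 86.

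**Step 2: results on which criterion and test part company** (108 per arm, chi-square without continuity correction).

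- 1 EMDR event against 9 in CAU: χ² = 216 × (1×99 − 9×107)² / (108 × 108 × 10 × 206) = 6.71, p = 0.01. The test favours EMDR, yet the criterion is failed.
- 3 EMDR events against 0: χ² = 216 × (3×108)² / (108 × 108 × 3 × 213) = 3.04, p = 0.08. The criterion is failed and the test is not significant.
- 0 against 0: the criterion is met, but the statistic has a zero in its denominator and cannot be computed.

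**Step 3: power to detect a tripling.** Sum the products of the two binomial probabilities over all tables with p < 0.05 and more events on EMDR, at 108 per arm.

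| EMDR vs CAU (assumed) | Power |
|---|---|
| 3% vs 1% | 16% |
| 6% vs 2% | 30% |
| 12% vs 4% | 61% |
| 15% vs 5% | 72% |

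**Step 4: what zero events would show.** The upper limit of the exact two-sided 95% interval for 0/n is 1 − 0.025^(1/n): 3.4% for n = 108 and 4.2% for n = 86.

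**Step 5: what the proposed measure would look like.** For 1 EMDR event against 0, the Newcombe 95% interval for the risk difference runs from −2.6 to +5.1 percentage points (n = 108) or −3.2 to +6.3 (n = 86).

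**The case against.** The best defence is that the definition should not be read alone. The Aim section says results are compared with CAU, the Safety section registers events in both groups, and the statistical section compares their prevalence. The definition could simply list the events that count, or describe the status of each woman. On that reading the sections form a chain. This stands as far as it goes: a reader might infer that the two rules flatly contradict each other, and the documents do not support that. A contradiction needs two statements the article never makes, that a single EMDR event makes the therapy unsafe and that a non-significant test makes it safe. What remains is the mismatch. Even on the kinder reading, nothing connects the comparison to the hypothesis that EMDR is safe.

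Three further points stand in part.

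- The figures depend on assumed rates. The exclusion of women with a recent psychiatric diagnosis, recent worsening or a recent suicide attempt should lower the background rate. At 0.5% a harmless therapy more often meets the criterion than fails it. At 4% to 5% the test would detect a tripling more often than not.
- Low power for rare harms is normal in a trial sized for efficacy. That is no fault in itself, but it does limit what a non-significant result can mean.
- Small expected counts might suggest that the chi-square test is invalid here. Enumeration at assumed background rates of 0.5% to 5% shows that the uncorrected test keeps its type I error at or below 5%. Fisher's test would mainly lose power to detect harm: 4% rather than 16% for 3% vs 1%, and 20% rather than 30% for 6% vs 2%.

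An acceptable rate or margin may be set in the full protocol or the SAP, so its absence from the article is not the point.

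**Conclusion.** The concern holds as a mismatch. Safety belongs to the stated main aim, its criterion is the absence of events, its analysis is a test of difference, and no decision rule joins them. At an assumed 1% background rate, a therapy with no effect on these events would fail the literal criterion in 66% of trials with 108 women per arm (100% − 34%). At background rates of 1% to 2%, the test would miss a tripling 70% to 84% of the time.

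A reader might infer that nothing in this plan could support the safety hypothesis. That goes too far: zero events in the EMDR arm would be real but limited support, excluding rates above 3.4% (108 women) or 4.2% (86). Nor do the documents show that a harmless therapy will probably be called unsafe, since that depends on a background rate they do not give. The point affects the safety conclusion only; the efficacy analysis is untouched.

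**What to change.** In the Aim section and under Primary study parameters, replace the absence criterion with one measure: the proportion of women with at least one listed event in each arm, with exact 95% confidence intervals, and the between-arm risk difference with a small-sample 95% interval such as Newcombe's. State that the safety conclusion will be worded from the upper confidence limits and that a non-significant test will not be reported as proof of safety. The chi-square test may stay; a move to Fisher's test is optional and corrects no error.

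The new measure needs a single list of events. The Aim section counts "crisis contacts for any of the aforementioned reasons", whereas the Safety section counts "contacts with healthcare providers in case of mental health crisis"; the two should be reconciled first. The Safety section also gives the monitoring to therapists in one arm and to researchers in the other. Confidence intervals do not remove any difference in detection that follows, so it should be stated beside the result.

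The cost is revised wording and a few lines of code, with no new data. The downside is a more modest safety claim.
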